#### Secondary outcomes

2.4.3

##### Functional impairment

2.4.3.1

The *Work and Social Adjustment Scale* (WSAS) (Mundt et al., 2002) is a brief, 5-item measure of perceived functional impairment in daily activities (e.g., work, family, interpersonal relations, social and private leisure activities, and home management). Items are answered on a 9-point scale, ranging from *not at all (0)* to *very severely (8)*. Higher scores reflect higher functional impairment. The WSAS presented good internal consistencies across several different health conditions (ranging between 0.70 and 0.94) (Pedersen et al., 2017). The WSAS’s psychometric properties, validity, and sensitivity to change have been established in several studies (Mundt et al., 2002). In Portuguese studies, the WSAS revealed good reliability (ranging between 0.87 to 0.93) (Carvalho et al., 2020;Trindade et al., 2021a,b,c).

##### General quality of life

2.4.3.2

The *EUROHIS-QOL 8-item index* (Power, 2003; Pereira et al., 2013) is a quality-of-life self-report measure comprising 8 items (general health, energy, daily living activity, overall quality of life, finances, social relationships, self-esteem, and home) obtained from the WHOQOL-Bref (The WHOQOL Group, 1994). Each item is answered using a 5-point Likert scale (matching the response scales used in the WHOQOL-bref). Higher scores indicate higher levels of quality of life. The EUROHIS-QOL 8-item index study, conducted in 10 different countries, showed an overall Cronbach’s alpha of 0.83 (Schmidt et al., 2005). In the Portuguese validation study, the scale presented a Cronbach alpha of 0.83 (Pereira et al., 2013).

##### Health-related quality of life

2.4.3.3

The *Inflammatory Bowel Disease Questionnaire – UK version* (IBDQ-UK) (Cheung et al., 2000) is the Anglicized 30-item version of the IBDQ (Guyatt et al., 1989; Irvine et al., 1994), an IBD-specific quality of life measure. The IBDQ-UK’s authors have modified the wording of some questions and simplified their response options. Items are rated on a 4-point scale ranging from “no, no at all/none” (0) to “on 8 – 14 days (i.e., more than every other day)/Yes, all of the time” (4). Respondents are asked about their experience with IBD and how it has impacted their lives during the preceding two weeks. The IBDQ-UK showed a very good reliability (Cronbach’s alpha of 0.94) in its original study (Cheung et al., 2000). A Portuguese version of this scale was created by the present research team for the purpose of the face-to-face LIFEwithIBD trial.

##### Chronic illness-related shame

2.4.3.4

The *Chronic Illness-related Shame Scale* (CISS) (Trindade et al., 2017a,b) is a 7-item self-report instrument that specifically targets shame related to the experience of having a chronic illness and/or its symptoms (e.g., “I feel isolated/alone due to my illness,” “I feel inferior and disregard myself because of my illness,” “I feel inadequate because of my illness and symptoms”). Items are answered using a 5-point Likert scale ranging from *never true* (0) to *always true* (4). Higher scores suggest higher levels of chronic illness-related shame. In the original study, conducted in Portugal, the CISS showed a very good reliability (α = 0.91) (Trindade et al., 2017a,b).

##### IBD symptom perception

2.4.3.5

The *IBD symptoms scale* (Trindade et al., 2017a,b) is a 16-item self-report scale designed to assess the perceived frequency of IBD symptoms during the previous month (e.g., fatigue, abdominal pain, bloating, flatulence, diarrhea, nausea or vomiting, fever, urgency). Items are rated on a 7-point scale, ranging from *never* (0) to a*lways* (6). Higher scores reveal higher levels of IBD symptom perception.

#### Usability, acceptability, and feasibility assessment

2.4.4

Participants in the experimental condition evaluated the quality of the eLIFEwithIBD intervention through several questions regarding the platform (e.g., audio files), and their perceived change on several different aspects (e.g., IBD symptoms, ability to self-regulate emotions, quality of life, perception of change by close ones). The following validated self-report measures were used to evaluate the usability, acceptability, and feasibility of eLIFEwithIBD:

##### System usability scale

2.4.4.1

The System Usability Scale (Brooke, 1996; Martins et al., 2015) is a 10-item self-report scale aimed to evaluate product and user interface usability (e.g., the confidence and ease of use of a platform). Items are rated on a 5-point scale ranging from *completely disagree* (1) to *completely agree* (5). Higher scores reveal more usability of a given digital product.

##### Acceptability (Aim) and feasibility (FIM) of intervention measures

2.4.4.2

The Acceptability and Feasibility Measures (Weiner et al., 2017) are 4-item self-report instruments that assess the extent to which an intervention is acceptable (e.g., “the intervention meets my approval”) and feasible (e.g., “the intervention seems easy to use”). Items are answered using a 5-point Likert scale ranging from *completely disagree* (1) to *completely agree* (5). Higher scores reveal greater acceptability and feasibility. Portuguese translations of the AIM and FIM were developed by the current research team for the purpose of this study, using forward and back translation methods.

### Statistical analysis

2.5

#### Sample size

2.5.1

An *a priori* power analysis for this study was performed. In the absence of meta-analytic evidence, we have used data from Wynne and colleagues (Ungaro et al., 2017) where moderate-to-large reductions in psychological distress were observed after baseline adjustment as a result of an ACT intervention in IBD. Given that there is little evidence to suggest the inferiority of internet-delivered interventions, we powered for an expected reduction in psychological distress of SMD = 0.75. Assuming an alpha of 0.05 and 80% power, we estimate that a total sample size of n = 58 would be required to power the primary analysis.

### Planned analyses

2.6

#### Data analysis

2.6.1

All analyses are planned as intent-to-treat (ITT) and will be examined using Jamovi statistical software (Jamovi, 2020), and R (R Core Team, 2021).

#### Primary outcome analysis

2.6.2

The primary outcome will be the psychological distress (DASS-21–depression, anxiety, and stress) measured at 9 weeks (immediately post-intervention) between the two intervention groups and adjusting for baseline scores using ANCOVA. We will examine the ANCOVA’s assumptions through standard tests and residual plots and perform transformations. The magnitude of the differences between-treatment groups will be expressed as the standardized mean difference.

#### Secondary analyses

2.6.3

Between-groups differences at 9 weeks will be examined for the following continuous outcomes: IBD symptom perception (IBDSS); psychological processes (CompACT, SCS-SF); chronic illness-related shame (CISS); work and social adjustment (WSAS); and quality of life (EUROHIS-QOL-8, IBDQ-UK). All analyses are to be conducted using ANCOVA with baseline values as a covariate.

#### Longitudinal outcomes

2.6.4

We will use Mixed Models of Repeated Measures (MMRM) to examine for Group Time interaction effects on each of the continuous outcomes from baseline, 9 weeks and 4 months; the DASS-21, the IBD symptom perception scale; SCS, CompACT, CISS, WSAS, EUROHIS-QOL-8, and IBDQ-UK.

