### Primary and secondary outcomes in the RCT

2.4

Participants completed self-report measures at three different times: baseline (T0), post-treatment (T1), and 4-month follow-up (T2) (Table 2).

**Table 2 tab2:** Schedule of enrollment, intervention, and assessments.

Study period					
	Enrollment	Allocation	Post-allocation		
Timepoint	-t2	-t1	t0	t1	t2

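### The longitudinal model takes baseline as a response and targets the group-by-time interaction, which uses baseline less efficiently than the 9-week ANCOVAs and does not by itself show a 4-month effect

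*Protocol article*

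**What the plan says.** The protocol article plans three layers of between-group analysis.

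- **Primary outcome analysis (2.6.2):** DASS-21 at 9 weeks, "adjusting for baseline scores using ANCOVA", with the difference expressed as a standardized mean difference.
- **Secondary analyses (2.6.3):** the other scales, also at 9 weeks. "All analyses are to be conducted using ANCOVA with baseline values as a covariate".
- **Longitudinal outcomes (2.6.4):** an MMRM whose stated target is the group-by-time "interaction effects on each of the continuous outcomes from baseline, 9 weeks and 4 months".

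The longitudinal section names no baseline covariate, no constraint on baseline means, no contrast at 4 months and no effect measure. Because the ANCOVAs stop at 9 weeks, the MMRM is the only planned comparison of the arms that includes the 4-month follow-up. The exploratory section adds reliable change indices correlated with demographics and within-group McNemar tests, neither of which compares the arms at 4 months.

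**The concern.** Two features of the stated longitudinal target deserve attention.

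First, baseline is handled differently from the 9-week analyses of the same people on the same scales. If baseline is a response and each arm has its own baseline mean, the group-by-time terms are differences between arms in raw change from baseline. Randomisation makes the true baseline means equal. ANCOVA uses that fact; a model with free baseline means does not. The 4-month effect would then be estimated less precisely than it need be, and the model's 9-week estimate would differ from the ANCOVA estimate whenever the arms differ by chance at baseline.

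Second, with two arms and three occasions the interaction has two degrees of freedom. Read as one overall test, it asks whether the arms' profiles differ anywhere. What a reader wants from the follow-up visit is whether the arms differ at 4 months and by how much.

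Precision is scarce here: 55 people were randomised (37 and 18) against a stated requirement of 58, and the Discussion expects that attrition may be high.

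**Working it through.** **Inputs from the article.** SMD 0.75, alpha 0.05 (taken as two-sided), 80% power and total n = 58 (Sample size); 37 and 18 randomised (Abstract); three occasions (Longitudinal outcomes).

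**Inputs assumed.** Unit variance at each occasion, one common correlation r between occasions, and no dropout. The article gives no correlation, so a range is shown.

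**The plan's own figure.** A two-sample t-test with SMD 0.75, two-sided 0.05, 80% power and equal arms needs 28.9, so 29 per arm and 58 in total. The stated n = 58 is reproduced. It relates to the primary analysis; the article states no size or power for the MMRM.

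**Step 1: variance of the 4-month contrast.** Let k = 1/37 + 1/18 = 0.0826.

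- Free baseline means (difference in change): variance = 2(1 − r)k.
- Baseline as covariate, or common baseline mean: variance = (1 − r²)k.
- Ratio = 2(1 − r)/(1 − r²) = 2/(1 + r).

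| r (assumed) | 2(1 − r) | 1 − r² | Ratio | Equivalent loss of sample, 1 − (1 + r)/2 |
|---|---|---|---|---|
| 0.5 | 1.00 | 0.75 | 1.33 | 25% |
| 0.6 | 0.80 | 0.64 | 1.25 | 20% |
| 0.7 | 0.60 | 0.51 | 1.18 | 15% |

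Over a wider range the ratio runs from 1.54 (r = 0.3) to 1.11 (r = 0.8). A generalised least squares calculation at r = 0.6 gives factors of 0.80 with free and 0.64 with constrained baseline means, matching the formulas.

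**Step 2: sensitivity to chance imbalance.** The standardised baseline difference between arms has SD √k = 0.29. A 1-SD imbalance separates the change-score estimate from the ANCOVA estimate by (1 − r) × 0.29: 0.14 SMD at r = 0.5 and 0.09 SMD at r = 0.7.

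**Step 3: what the overall interaction can show.** The 2-df test depends on its noncentrality. For a raw effect d at both follow-up visits, at 9 weeks only, or at 4 months only, the noncentrality is the same: 2d²/[3(1 − r)k]. With r = 0.6 and d = 0.60 (0.75 on the baseline-adjusted scale, so 0.75 × √0.64) it is 0.24/(0.4 × 0.0826) = 7.27, and power is 65% in all three cases. The test cannot tell a lasting effect from one that has gone by 4 months.

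**Step 4: power for the 4-month contrast, conditional on r and on the scale of the SMD** (t-test approximation, 53 df, 37 versus 18).

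| r (assumed) | SMD 0.75 read as baseline-adjusted: adjusted / change | SMD 0.75 read as raw: adjusted / change |
|---|---|---|
| 0.5 | 73% / 60% | 84% / 73% |
| 0.6 | 73% / 63% | 89% / 82% |
| 0.7 | 73% / 66% | 95% / 91% |

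The Sample size section says the source reductions were seen after baseline adjustment, which favours the first reading without settling it. The variance ratio in Step 1 is the same under both.

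**The case against.** The strongest case on the other side is that most of this is not stated in the article.

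- **A reader might infer that the model throws baseline adjustment away.** It does not. With baseline as a response, the interaction terms are differences in change from baseline, so baseline is subtracted and the estimate is unbiased under randomisation. What remains is a loss of efficiency.
- **Free baseline means are inferred.** The text does not say whether they are free or constrained. A model with a common baseline mean also has three response occasions and group-by-time terms, and it carries no loss. This stands: the loss applies to the usual fit, not to every model the wording allows.
- **A single 2-df test is inferred.** The text speaks of interaction effects in the plural and excludes no visit-specific contrast; a 4-month contrast can be taken from the same fitted model. Nor does the text say that the model exists to estimate the 4-month effect.
- **Details may sit in a plan not shown.** Parameterisation and contrasts are commonly left there. This limits the weight of the point. It does not remove it, because the article does fix the target and the response occasions.
- **Baseline as a response has a merit.** It keeps participants who have only T0, in line with the stated use of all data collected. This stands and shapes the remedy.
- **The analysis is not primary.** The study describes itself as a feasibility trial of preliminary efficacy, and no power is claimed at 4 months.

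**Conclusion.** The point holds as a modest improvement to a non-primary analysis. The article makes the group-by-time interaction over three occasions, baseline included, its longitudinal target. With free baseline means, the 4-month effect is an unbiased but less efficient difference in change scores, with variance 1.33, 1.25 or 1.18 times that of the baseline-adjusted contrast at r = 0.5, 0.6 or 0.7. This departs from the baseline handling in the 9-week ANCOVAs, and a significant overall interaction would not establish a difference at 4 months.

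The size rests on assumed equal correlations, no dropout and free baseline means. The power figures rest further on how the SMD of 0.75 is scaled, so they are illustrations only. The documents do not support saying that the planned estimate is biased, that baseline is ignored, or that the trial will report only an overall test.

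**What to change.** In the Longitudinal outcomes section, specify one of two models:

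1. **Preferred:** keep baseline, 9 weeks and 4 months as responses, constrain the two arms to a common baseline mean, and allow group differences at 9 weeks and 4 months. This recovers the baseline-adjusted precision and keeps participants with only T0.
2. **Alternative:** use 9 weeks and 4 months as responses, with baseline, baseline-by-time, group and group-by-time as fixed effects. With complete data the precision is the same, but participants with only T0 drop out.

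In either case use an unstructured covariance, and name the between-group difference at 4 months, with its 95% CI, as the result of this analysis in place of an overall interaction p-value.

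The cost is a sentence or two of specification. No new data are needed. The only price is the loss of T0-only participants under the second model.

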#### Exploratory outcomes

2.6.5

Reliable change indices between baseline and follow-up points will be calculated for all outcomes and correlated with demographics to examine for subgroup efficacy predictors. The cut-off for clinically significant change is generally accepted as ±1.96 (R Core Team, 2021). For exploratory analyses focused upon proportionate data, such as comparisons of mood dysfunction outcomes, McNemars’ test can be used to examine within-group differences across time points.

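### Correlating reliable change indices with demographics finds predictors of change, not predictors of efficacy, because the stated method compares no arms

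*Protocol article*

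**What the plan says.** Section 2.6.5 of the protocol article says that reliable change indices, from baseline to each follow-up, will be computed for every outcome and "correlated with demographics to examine for subgroup efficacy predictors". The same section adds that "The cut-off for clinically significant change is generally accepted as ±1.96", which is a criterion for change within one person. It also says that for proportions McNemar's "test can be used to examine within-group differences across time points", again within a group.

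The sentence does not say whether the correlations are pooled over arms or taken by arm. It names no comparison of correlations between arms and no arm-by-demographic term. Sections 2.6.2 and 2.6.3 specify between-arm ANCOVAs adjusted for the baseline score, without a moderator. The only interaction in the article is in section 2.6.4, where mixed models are used "to examine for Group Time interaction effects on each of the continuous outcomes from baseline, 9 weeks and 4 months". That examines how the average arm difference develops over time, not how it differs between kinds of patient.

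**The concern.** The section ties a named method to a named inference, and the method cannot support the inference. A participant's change score is the sum of what would have happened under usual care and whatever the programme added. A demographic can be related to the first part alone. The Introduction describes IBD as a condition that flares and remits, so change without treatment is to be expected. A demographic related to baseline distress will also be related to change through regression to the mean.

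If the sentence is followed as written, prognostic factors will be reported as markers of who benefits. The Conclusion presents this trial as a possible starting point for larger studies, so mislabelled predictors could shape who is recruited or offered the programme next. The exposure is broad. The indices cover all outcomes at both follow-up points, and section 2.6.4 lists eight instruments, so 8 × 2 = 16 correlations are implied for each demographic.

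**Working it through.** **Inputs from the article.** 37 experimental and 18 control participants (Abstract, Methods); expected effect SMD 0.75 (section 2.5.1). No figure is attached to the predictor analysis, so there is none to reproduce for it. The one related figure, a total of 58, is recovered by a two-sided 5% two-sample t-test with 80% power and equal arms (29 per arm), but it has no bearing on this point.

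**Input assumed.** The correlation *r* between a demographic and change for reasons unrelated to treatment. The article gives no value; the range 0 to 0.5 is shown.

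**Step 1: what the correlation estimates.** A reliable change index is change divided by a constant, so its correlation with a demographic equals that of raw change. Write change = −0.75·A + g·X + d·A·X + error, with A the arm (1 = intervention) and X the standardised demographic. Then *g* is the prognostic slope and *d* is the effect modification, the quantity meant by an efficacy predictor.

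- Intervention arm only: slope g + d.
- Pooled: slope about g + (37/55)·d.
- Arm-by-demographic interaction: d.

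Only the third isolates *d*.

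**Step 2: no effect modification (d = 0), approximate calculation at r = 0.4.**

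- Pooled: the arm difference adds variance 0.75² × (37 × 18)/55² = 0.124. The pooled correlation is 0.4/√1.124 = 0.377. Fisher's z is 0.397, and 0.397 × √(55 − 3) = 2.86. The chance of significance is about Φ(2.86 − 1.96) = 0.82.
- Intervention arm only: Fisher's z of 0.4 is 0.424, and 0.424 × √(37 − 3) = 2.47. The chance of significance is about Φ(2.47 − 1.96) = 0.69 to 0.70.

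**Step 3: simulation.** 8,000 trials per row, d = 0, two-sided 5% tests. Share significant:

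| r | Pooled correlation | Intervention arm only | Interaction test |
|---|---|---|---|
| 0 | 4.8% | 4.5% | 4.5% |
| 0.2 | 28% | 22% | 4.9% |
| 0.3 | 55% | 44% | 5.1% |
| 0.4 | 83% | 71% | 4.8% |
| 0.5 | 96% | 89% | 4.9% |

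The row at 0.4 agrees with step 2. A second set of 4,000 trials fixed the slope at 0.4 with residual SD 1, so that the within-arm correlation is 0.4/√1.16 = 0.37. It gave 78%, 64% and 5%; a slope of 0.3 gave 54%, 41% and 5%. At a slope of 0.1 the two correlations are significant in about 11% and 9%.

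**Step 4: the reverse error.** Take g = −0.4 and d = +0.4. The intervention-arm slope is −0.4 + 0.4 = 0, and that correlation is significant in 4.8% of trials. The pooled slope is about −0.4 + (37/55) × 0.4 = −0.13, opposite in sign to *d*, and significant in 16%. The interaction test is significant in 29%.

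**Step 5: precision of the right quantity.** With residual SD 1, the standard error of *d* is about √(1/37 + 1/18) = 0.29, so a 95% interval extends about 1.96 × 0.287 = 0.56 SD per SD on either side. Simulated power for d = 0.5 is about 38%.

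**The case against.** The strongest reply is that the sentence is one line of a condensed article and leaves the handling of arms open. Correlations could be run in each arm and then contrasted, which would address effect modification. That reading is possible, but nothing in the article states it, and the surrounding methods in the same section are within-person or within-group. The point is not that detail is missing. The method named does not match the purpose named, and an analysis plan that followed the sentence would carry the mismatch forward.

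Three further objections carry weight. First, the percentages depend on an assumed prognostic correlation for unnamed demographics; at 0 to 0.1 the excess is nil or small, so no single figure is an expected error rate for this trial. Second, the simulation illustrates a definition: the correlation test validly detects an association with change, and the result becomes false only when labelled efficacy. It also draws change directly and does not model regression to the mean. Third, the section is labelled exploratory, the trial aims at preliminary efficacy, and an interaction test with 37 against 18 has little power. These limit the importance of the point. They do not make the correlation an estimate of differential benefit, and low power for the right quantity is no reason to test a different one.

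**Conclusion.** The concern holds. As written, section 2.6.5 would report predictors of change as predictors of efficacy. The mismatch needs no numerical assumption. Its size does: with no effect modification and a prognostic correlation of 0.2 to 0.5, a spurious predictor appears in 28% to 96% of trials pooled and in 22% to 89% in the intervention arm, falling to about 5% at zero correlation, against about 5% for an interaction test at every value. These figures apply to one demographic and one outcome, with 37 and 18 participants all followed up. The primary, secondary and longitudinal comparisons are untouched, so this should be corrected but does not threaten the main result.

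**What to change.** For each demographic, listed in advance, fit the baseline-adjusted ANCOVA already planned, on the raw score rather than the reliable change index, with an arm-by-demographic interaction. Report the interaction estimate with its 95% confidence interval and label it exploratory. If the correlations with reliable change indices are kept, describe them as predictors of change and remove the reference to efficacy.

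The cost is wording and a few lines of code; no new data are needed. The drawback is wide intervals, roughly ±0.56 SD per SD of the demographic at full follow-up and wider with attrition. That is the precision this sample has for the question.

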**Methods:**

The eLIFEwithIBD intervention is an adaptation of the LIFEwithIBD programme (delivered through an in-person group format) and entails an ACT, mindfulness, and compassion-based intervention designed to be delivered as an e-health tool for people with IBD. This protocol outlines the structure and contents of the eLIFEwithIBD intervention. Participants were recruited by an advertisement on the social media platforms of Portuguese Associations for IBD in January 2022. A psychologist conducted a brief interview with 80 patients who were interested in participating. Fifty-five participants were selected and randomly assigned to one of two conditions [experimental group (eLIFEwithIBD + medical TAU; *n* = 37) or control group (medical TAU; *n* = 18)]. Outcome measurement took place at baseline, post-intervention, and 4-month follow-up. All analyses are planned as intent-to-treat (ITT).

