The present study aims to examine the acceptability, usability, and preliminary efficacy of an online intervention – the eLIFEwithIBD intervention - on the improvement of psychological distress and other psychosocial indicators in IBD. This intervention was be adapted from a face-to-face group intervention (LIFEwithIBD) (Yin and Neyens, 2020) previously tested in patients with IBD, and is the first to incorporate ACT, mindfulness and compassion components through an online intervention targeting this population. This intervention (eLIFEwithIBD + Treatment and Usual [TAU])‘s superiority in improving psychological distress, quality of life, work and social functioning, IBD symptom perception, illness-related shame, psychological flexibility, and self-compassion will be compared to TAU. This paper presents the structure and contents of the eLIFEwithIBD intervention as well as the design of this Randomized Controlled Trial (RCT).

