### Recruitment and data collection

2.2

This trial is registered at ClinicalTrials.gov (Identifier: NCT05405855). The planning and execution followed the American Psychological Association (Ferreira et al., 2019) and the World Medical Association’s Declaration of Helsinki (American Psychological Association, 1992) guidelines. Authorization for sample recruitment was obtained from the Faculty of Psychology and Education Sciences of the University of Coimbra. Recruitment was facilitated by advertisements on social media by Portuguese Associations for IBD in January 2022, which included a link to a registration questionnaire. Individuals interested in participating were screened by a psychologist through a short interview (to present the aims of the study, obtain informed consent, and assess eligibility), conducted by videoconference or phone call. Eligible participants were asked to complete baseline questionnaires (T0) via an online survey.

After completing the baseline assessment (T0), participants were randomly assigned (computer-generated random allocation, ratio 2:1) (World Medical Association, 2013) to the experimental condition (eLIFEwithIBD intervention + TAU) or the control condition (TAU). Participants in both conditions were informed about their assigned treatment condition and then, participants in the experimental condition had access to the eLIFEwithIBD platform. After the intervention (T1) and in the 4-month (T2) follow-up, participants in both conditions received notifications via email to complete self-report questionnaires again, via an online survey. Participants in the control condition will receive the intervention after completing the last assessment of the study (T2). Figure 1 shows the CONSORT flow diagram.

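### The only method named for the exploratory binary mood outcomes is a within-arm McNemar test, which does not compare the randomised groups and has very unequal power in arms of 37 and 18 (minor).

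*Protocol article*

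**What the plan says.** Section 2.6.5 (Exploratory outcomes) deals with binary data in one sentence. It opens "For exploratory analyses focused upon proportionate data, such as comparisons of mood dysfunction outcomes" and goes on to say that McNemar's "test can be used to examine within-group differences across time points". The wording permits the test and does not require it.

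The aim in the Introduction is comparative. It lists psychological distress and other indicators, and says that the intervention's superiority in improving them, down to "illness-related shame, psychological flexibility, and self-compassion will be compared to TAU".

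The methods that compare the arms are set out for continuous scores. Sections 2.6.2 and 2.6.3 use ANCOVA at 9 weeks with the baseline value as covariate. Section 2.6.4 uses an MMRM with a group-by-time term for the continuous outcomes at baseline, 9 weeks and 4 months. None of these sections mentions proportions.

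Allocation was by "computer-generated random allocation, ratio 2:1" (section 2.2). The Abstract gives the arms as "experimental group (eLIFEwithIBD + medical TAU; *n* = 37) or control group (medical TAU; *n* = 18".

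**The concern.** McNemar's test asks whether the proportion with a condition changed between two occasions in the same people. Run within an arm, it cannot separate the intervention's effect from natural course or regression to the mean. Those influences act on both arms, and only a between-arm contrast removes them. The Introduction itself describes IBD as relapsing and remitting.

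The unequal allocation adds to this. The intervention arm is about twice the size of the control arm, so the same true change is much more likely to reach p < 0.05 there. Someone reading the two p-values side by side could see an effect where the arms do not differ. What is at stake is the reading of an exploratory proportion result, in a trial that its Conclusion presents as a possible starting point for larger studies. The primary comparison is not at stake.

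**Working it through.** **Inputs from the article.** Arm sizes are 37 and 18 (Abstract). Alpha is 0.05 (section 2.5.1: "Assuming an alpha of 0.05 and 80% power"); the number of sides is not stated, and I take two.

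**The plan's own figure.** The article gives no rate, cut-off or power for a binary outcome, so there is nothing to reproduce on this point. Its one planning figure, a "total sample size of n = 58 would be required to power the primary analysis", concerns the continuous primary outcome at SMD 0.75. A two-sided two-sample t-test with equal arms gives it: 29 per arm, total 58, power 80.1%. It does not enter the calculation below.

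**Assumptions.** Let p10 be the share of all participants in an arm who move from dysfunction to none, and p01 the share who move the other way. Both are set equal in the two arms, so there is no treatment effect. Data are complete and the test is exact.

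**Step 1. Smallest significant result.** With m discordant pairs all in one direction, p = 2 × 0.5^m. For m = 5 this is 0.0625, and for m = 6 it is 0.031. So at least six discordant pairs are needed. That is 6/18 = 33% of the control arm but 6/37 = 16% of the intervention arm.

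**Step 2. Power within an arm of size n.** The number of discordant pairs m is binomial (n, p10 + p01). Given m, the number improving, b, is binomial (m, p10/(p10 + p01)). Power is the total probability of outcomes with b > m − b and 2 × P(Bin(m, ½) ≤ min(b, m − b)) ≤ 0.05.

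**Step 3. Significant in one arm only.** The arms are independent, so P(intervention only) = P37 × (1 − P18) and P(control only) = P18 × (1 − P37). For 25% improving and 5% worsening, 0.522 × (1 − 0.151) = 0.443 and 0.151 × (1 − 0.522) = 0.072.

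| Improve / worsen, both arms | Power, n = 37 | Power, n = 18 | Intervention only | Control only |
|---|---|---|---|---|
| 10% / 5% | 3.8% | 0.3% | 3.8% | 0.3% |
| 15% / 5% | 15.1% | 2.2% | 14.8% | 1.8% |
| 20% / 5% | 32.7% | 6.9% | 30.4% | 4.7% |
| 20% / 2% | 56.3% | 10.3% | 50.5% | 4.5% |
| 25% / 5% | 52.2% | 15.1% | 44.3% | 7.2% |
| 25% / 2% | 76.4% | 22.0% | 59.5% | 5.2% |
| 30% / 5% | 69.6% | 26.0% | 51.4% | 7.9% |
| 30% / 3% | 82.7% | 32.9% | 55.5% | 5.7% |
| 35% / 5% | 82.7% | 38.4% | 50.9% | 6.7% |

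For 20-35% improving and 2-5% worsening, the result runs from about 30% (20/5) to about 60% (25/2); the other pairs in that region shown here lie between 44% and 56%.

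**Step 4. Sensitivity.** More worsening lowers the figure: 20/10 gives 11.6% and 30/10 gives 34.3%. So do fewer completers: with an assumed 26 and 13, 25/5 falls from 44% to 31%. The uncorrected chi-square version of the test gives 22% for 15/5 and 10% for 10/5.

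**Step 5. A single illustration.** Suppose 10 of 37 improve and 2 worsen: p = 2 × (1 + 12 + 66)/4096 = 0.039. Suppose 5 of 18 improve and 1 worsens: p = 2 × (1 + 6)/64 = 0.22. The improving proportions are 27% and 28%, and Fisher's exact test between the arms gives p = 1.0.

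**Step 6. A direct comparison.** With 37 v 18 and a common true prevalence of 10-40%, a two-sided between-arm test is falsely significant in 2.4-3.8% of trials (Fisher) or 3.8-5.2% (Pearson chi-square).

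**The case against.** Four things can be said in favour of the plan.

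First, the sentence says the test may be used, labels the analysis exploratory and labels the comparison within-group. McNemar's test is correct for paired proportions over time. This stands. A reader might infer that the plan commits the binary mood outcomes to this test, but the wording does not go that far.

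Second, a reader might infer that significance in one arm and not the other will be presented as efficacy, or that the protection of randomisation is given up. The documents do not support either. Nowhere is such an inference planned. Every outcome in the stated superiority aim is measured on a continuous scale and compared between arms by ANCOVA and MMRM, and depression, anxiety and stress are themselves the primary outcome.

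Third, a between-arm model for an exploratory binary endpoint may sit in an analysis plan that is not shown. This stands only in part. Missing detail would be no finding, but the article does name a method, introduces it for comparisons of mood dysfunction, and the method does not compare the arms.

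Fourth, the change rates are assumed. The trial excluded major depressive disorder and suicidal ideation, so a 25% shift out of dysfunction may not be reached, and the Discussion expects high attrition. This stands. It is why the size is given as a range, and why the artefact cannot be called expected in general: at 10% improving and 5% worsening it is about 4%.

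**Conclusion.** The point holds as a minor one. The one method the article names for binary mood outcomes does not address the trial's comparative question, and the 2:1 allocation makes a side-by-side reading of two within-arm p-values lopsided. With identical change in both arms, significance in the intervention arm alone is common when net improvement is about 15 points or more (30% to 60% in the 20-35% / 2-5% region). It is modest at 15/5 and rare at 10/5. These figures rest on assumed rates, the exact test at two-sided 0.05 and complete data. The harm arises only if the two p-values are read against each other, which the article neither plans nor rules out. The primary ANCOVA, the secondary ANCOVAs and the MMRM are untouched.

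**What to change.** In section 2.6.5, replace the McNemar sentence with a direct comparison of the arms for the binary mood outcomes at 9 weeks and at 4 months. One suitable choice is logistic regression of dysfunction on arm, adjusted for baseline DASS-21 score and penalised (Firth-type) if events are sparse. Report the odds ratio or risk difference with its 95% confidence interval, labelled exploratory. Present within-arm changes descriptively, and state that no between-arm conclusion will be drawn from them.

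No new data, visits or participants are needed. The costs are a few sentences and a little code, a definition of mood dysfunction with its cut-off set before the outcomes are compared by arm, and an estimate that will be imprecise with 37 and 18 participants. The continuous ANCOVA and MMRM should remain the main evidence on mood.
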